### Summary study protocol

PASS is a multicenter prospective, randomized, phase III, open-label, blinded end-point superiority trial (PROBE) of standard care with preventive ceftriaxone treatment compared to standard care without preventive ceftriaxone. Adult patients with stroke (both ischemic and hemorrhagic), a score ≥1 on the National Institutes of Health Stroke Scale (NIHSS) and stroke onset within 24 hours were included
[8]. Patients were excluded in case of infection at admission, use of antibiotics within 24 hours before admission, previous hypersensitivity or anaphylaxis to cephalosporins or penicillin, subarachnoid hemorrhage, pregnancy or when death seemed imminent. Patients were randomly assigned to either ceftriaxone at a dose of 2 g, given every 24 h intravenously for 4 days, in addition to stroke-unit care, or standard stroke-unit care without preventive antibiotic therapy. Randomization was performed through ALEA (online software for randomized trials;
https://nl.tenalea.net/amc/ALEA/Login.aspx) and is based on a uniform distribution; weight of the arms is equal (1:1). Randomization is stratified according to study center (academic hospital, large non-academic hospital, or small non-academic hospital) and stroke severity (score on NIHSS 1 to 9 or >9) and performed by using random blocks with a maximum block size of 6; blocks of 2, 4 and 6 are made per stratum combination

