**Flow-chart of patients.**

### Definition of intention-to-treat and per-protocol population

Main analysis will be performed according to the intention to treat (ITT) principle. The safety analysis will be performed in a per protocol (PP) analysis. If a patient was by fault randomized more than once, the first randomization outcome was used. Patients who withdrew consent directly after randomization (that is, before treatment was initiated in those randomized for ceftriaxone in addition to standard care, or within 6 hours after randomization in those randomized for standard care) will be excluded from analysis. Patients with protocol deviations in eligibility are included in the ITT analysis and will be tabulated (Table 
1). Patients not receiving their allocated treatment due to instantaneous crossover are considered protocol violations; these patients will be included in the ITT population. PP analysis will exclude patients for whom protocol deviations in treatment and eligibility were made (see protocol deviations in eligibility and protocol deviations in treatment).

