#### Infection rate during hospital admission

The total number of patients diagnosed with one or more infection(s) during hospital admission will be reported, as well as the total number of infections. Infections will be reported according to subtypes pneumonia, urinary tract infection and other infection. Infection will be assessed in two ways. First, the infection will be diagnosed in the clinical setting by the treating physician and registered as pneumonia, urinary tract infection or other infection. The clinical diagnosis of infection will be used for the primary analysis. Suspected infections without diagnostics being performed are also recorded and reported as such (for example, in a patient with a palliative care policy). Second, infection will be categorized by two infectious disease specialists who are blinded for treatment allocation, using the modified criteria of the Centers for Disease Control and Prevention (CDC criteria)
[12]. For this second categorization, patients with fever, new onset delirium or clinical diagnosis of infection during hospital admission will be reviewed. For this purpose, data on the diagnostic procedures during admission as recorded in the Case Record Form (CRF) will be used. For the diagnosis of pneumonia and urinary tract infection prespecified algorithms will be used based on the CDC-criteria (Figures 
2 and
3). Patients with a positive blood culture or a positive culture from the presumed site of infection, other than the lungs or urine, with a clinically relevant pathogen will be diagnosed as ‘other infection.’ Patients will be categorized as having confirmed pneumonia, urinary tract infection, or other infection. Only bacterial infections will be assessed since preventive antibiotic therapy aims to reduce these infections. Infection with *Clostridium difficile* is reported as a treatment complication. Case definition of this infection is diarrhea plus a positive *C. difficile* toxin test. Clostridium infection was diagnosed by the treating physician and was reviewed by the expert panel.

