### Subgroup analysis of primary and secondary outcomes

We will perform the following sub-group analyses for the primary outcome: stroke type (infarction or hemorrhage), stroke severity (NIHSS 1 to 9 or NIHSS 10 to 30), time between stroke symptoms and start of the antibiotic treatment (0 to 12 h versus 12 to 24 h) and age. For the subgroup analysis of primary analysis of primary outcome, the single OR from the proportional odds model will be calculated for each subgroup separately. For the subgroup analysis of secondary analysis of primary outcome, we will tabulate the results and analyze them using the chi-squared test and presented as OR and 95% CI ((Table 
7: subgroup analysis of primary outcome). In addition to these predefined subgroup analyses, we will perform a larger set of exploratory additional analyses. For secondary outcomes, we will perform all the previous mentioned subgroup analyses (stroke type, severity, time to treatment, and age). In addition we will perform analysis on presence of a swallowing disorder, respiratory tract infections, and a urinary catheter.

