### Discussion

The aim of our study is to investigate whether preventive antibiotic therapy improves functional outcome by reducing the number of infections in acute stroke patients. With this SAP, we present the analyses that will be published in the primary publication. By publishing the statistical analysis plan before knowledge of any outcome, we stimulate transparency of scientific conduct and allow others to add timely suggestions for additional analyses.

Patients in the acute phase of stroke are at risk for infections. A systematic review and meta-analysis of 87 studies showed that infections complicate stroke in 30% of all stroke patients. Pneumonia was associated with mortality with an OR of 3.62 (95% CI 2.80 to 4.68)
[3]. The effect of preventive antibiotic therapy on outcome in stroke patients has been investigated in few studies. Two meta-analyses of these studies showed that preventive antibiotic therapy reduced the number of infections
[4, 5]. The proportion of patients who died and the number of disabled patients were not significantly reduced, but numbers of included patients were small.

The PROBE design with open-label preventive antibiotics might introduce detection bias for infection. Physicians are aware of the treatment allocation, which potentially influences decisions on nonscheduled treatment (that is, the detection and treatment of patients with infection). This might influence the outcome measure of infection rate. To control for this bias, we will provide a secondary judgement of infection diagnosis by a blinded expert panel, according to CDC criteria. The CDC criteria are restrictive and use ancillary investigations such as blood tests, chest X-rays and culture results to confirm the diagnosis of infection. In clinical practice, for a stroke patient with fever, a cough and abnormalities on auscultation, a physician will often not wait for culture results or refrain from treating pneumonia when a chest X-ray does not (yet) show a consolidation.

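### Respiratory tract infection, an event that arises after randomization and that ceftriaxone is meant to prevent, is planned as a subgroup factor for the secondary outcomes

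*SAP article*

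**What the plan says.** In *Subgroup analysis of primary and secondary outcomes* the SAP article names the subgroups for the primary outcome and then turns to the secondary ones: "For secondary outcomes, we will perform all the previous mentioned subgroup analyses (stroke type, severity, time to treatment, and age"). The next sentence extends the list: "In addition we will perform analysis on presence of a swallowing disorder, respiratory tract infections, and a urinary catheter". It gives no time of assessment for the three items and no restriction to baseline status.

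Four other places bear on the respiratory infection item:

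- *Summary study protocol*: "Patients were excluded in case of infection at admission".
- *Definition of intention-to-treat and per-protocol population*: "Patients with protocol deviations in eligibility are included in the ITT analysis and will be tabulated". Table 1 has a row for infection at admission.
- *Infection rate during hospital admission*, a secondary outcome: "Infections will be reported according to subtypes pneumonia, urinary tract infection and other infection". The treating physician's diagnosis is the main one. A blinded two-person panel classifies infection a second time by modified CDC criteria.
- *Discussion*: "Two meta-analyses of these studies showed that preventive antibiotic therapy reduced the number of infections". On open-label care it adds: "Physicians are aware of the treatment allocation, which potentially influences decisions on nonscheduled treatment".

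Dysphagia is in the baseline list and in Table 3. Urinary catheter and respiratory infection are in neither.

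**The concern.** A subgroup comparison keeps the protection of randomization only if treatment cannot influence who is in the subgroup. Respiratory infection fails that condition here, because preventing infection is the purpose of ceftriaxone. Patients infected despite ceftriaxone may differ in prognosis from patients infected under standard care, and the same holds for the uninfected patients in each arm. A difference in death or stay within a stratum could then reflect who was selected into it.

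At stake is the reading of the secondary results. The Discussion says that the article sets out the analyses for the primary publication. A mortality contrast among infected patients could appear there as prespecified and be taken as evidence of harm or benefit.

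**Working it through.** The plan states no figure on this point, so there is none to reproduce. The check has three parts.

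**1. The passages side by side.**

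- *Timing.* Infection at admission excludes a patient. A respiratory infection in an eligible patient therefore comes later. The exception is a patient randomized in breach of that criterion, who stays in the intention-to-treat population.
- *Effect of treatment.* The Discussion cites meta-analyses showing fewer infections with preventive antibiotics, so membership is expected to differ by arm.
- *Ascertainment.* The main diagnosis of infection is made by physicians who know the allocation. The SAP does not say whether that diagnosis or the panel's would define the subgroup.
- *Overlap.* Pneumonia is a subtype of the infection outcome. If one diagnosis defines both subgroup and outcome, every patient in the infected stratum has the event in both arms and no odds ratio can be estimated.
- *Method.* The tests named for secondary outcomes are chi-square, t-test and Mann-Whitney. None allows for a factor affected by treatment.

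**2. Two-class illustration (all inputs assumed).** Take 30% frail patients (death risk 40%) and 70% robust patients (death risk 5%), with no effect of treatment or infection on death. Whole-trial mortality is 0.3×0.40 + 0.7×0.05 = 15.5% in both arms. Control infection risk is 40% in frail and 10% in robust patients. Death among infected controls is (0.3×0.40×0.40 + 0.7×0.10×0.05)/(0.3×0.40 + 0.7×0.10) = 0.0515/0.190 = 27.1%.

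The result on ceftriaxone depends on how the infection risk falls:

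- *Larger relative reduction in robust patients* (32% / 4%; relative risks 0.8 and 0.4): 0.0398/0.124 = 32.1%, OR (0.321/0.679)/(0.271/0.729) = 1.27.
- *Common odds ratio of 0.6* (28.6% / 6.25%): 0.0365/0.1295 = 28.2%, OR 1.05.
- *Common relative risk of 0.5* (20% / 5%): 0.02575/0.095 = 27.1%, OR 1.00. In the uninfected stratum, death is then 0.1035/0.81 = 12.8% in controls and 0.12925/0.905 = 14.3% on ceftriaxone, OR 1.14.

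**3. Continuous frailty.** Let u be standard normal, with

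logit P(infection) = a + b·u + ln(OR_inf) for ceftriaxone

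logit P(death) = d + b·u + ln(3.62) if infected.

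Treatment acts on death only through infection. The 3.62 comes from the Discussion ("Pneumonia was associated with mortality with an OR of 3.62 (95% CI 2.80 to 4.68")); using it as an odds ratio at fixed frailty is an assumption. Also assumed are a control respiratory infection rate of 7%, 10% or 15%, OR_inf of 0.4 or 0.6, control mortality of 12%, and 2,550/2 = 1,275 patients per arm. The ranges below run over the six combinations of infection rate and OR_inf.

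| b | Death OR, infected | Death OR, uninfected | Death OR, all randomized |
|---|---|---|---|
| 0 | 1.00 | 1.00 | 0.861 to 0.951 |
| 1 | 1.037 to 1.100 | 1.027 to 1.078 | 0.854 to 0.946 |
| 2 | 1.131 to 1.293 | 1.075 to 1.221 | 0.875 to 0.954 |

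With shared frailty (b above 0), both strata point towards harm while the comparison of all randomized patients shows benefit. The infected strata are also small and unequal: at a 10% control rate, 128 controls against 54 to 91 ceftriaxone patients.

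**The case against.** *The wording is loose.* The sentence speaks of analysis on the presence of three items. It names no within-stratum test, and neither Table 4 nor Table 7 has rows for them. They could be meant as outcomes. The heading and the preceding sentence make subgroups the natural reading, though. As outcomes, the sentence would largely repeat pneumonia and would add two items that are outcomes nowhere else in the article. The objection justifies saying that this is the natural reading; it does not remove the point.

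*The size is not established.* A reader might infer from the 1.27 that an odds ratio of that order is to be expected. The documents do not support this. The figure needs a larger relative reduction in robust than in frail patients, and it falls to about 1.05 or to 1.00 under the other patterns shown. This objection stands, and only a range can be given.

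*Circularity is partial.* A reader might infer that every infection outcome is 100% in the infected stratum. A clinically diagnosed case need not meet the panel's stricter criteria, urinary and other infections are separate subtypes, and death, stay and antibiotic use are not circular at all. This also stands.

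*Not every case arises after randomization.* Patients wrongly included with infection at admission stay in the analysis. They are probably few, but the statement needs that exception.

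*The other two factors differ.* It is tempting to reject all three together. Dysphagia is already a baseline variable. For the catheter the article gives no recording time, and the protocol or case record form may supply one. Placement after randomization is a possibility, not something the article states.

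**Conclusion.** The point holds for respiratory tract infection as a subgroup factor. The conclusion rests on the exclusion criterion, the aim of the treatment and the definition of the infection outcome, all in the article, and on the natural reading of one loosely worded sentence. Comparisons of the arms within these strata are not randomized and can be biased. For any infection or pneumonia they are circular where the same diagnosis is used twice.

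The size cannot be taken from the documents. Under the assumed inputs, the odds ratio for death among infected patients lies between 1.00 (no shared frailty, or an equal relative reduction in infection across frailty levels) and about 1.3. Among uninfected patients it reaches about 1.2.

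Severity is minor. These are additional analyses of secondary outcomes, and the preceding text announces a wider exploratory set. A reader might infer that the trial's main conclusions are threatened. They are not: the ordinal analysis of the mRS, the sample size and the whole-trial comparisons of infection and death do not use these strata.

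**What to change.** - Delete respiratory tract infection as a subgroup factor. Alternatively, report outcomes by infection status as descriptive, non-randomized data, without a treatment-effect estimate or P value.
- State that swallowing disorder means the status recorded at baseline.
- Use urinary catheter as a subgroup factor only if it was recorded before or at randomization; otherwise drop it.
- Add one sentence that every subgroup factor must be fixed before or at randomization.
- If the infection pathway is of interest, a mediation analysis of all randomized patients, labelled exploratory, is an option but not a requirement.

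The cost is a change of wording and at most the loss of one or two additional analyses. No new data are needed, and the primary analysis and sample size stay as they are.

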**Table 7 Tab7:** **Subgroup analysis of primary outcome**

	Ceftriaxone + standard care (n = …)	Standard care (n = …)	***P***	OR 95% CI
Favorable outcome (mRS* 0 to 2) - % n/N				
- Ischemic stroke				
- Hemorrhagic stroke				
- Transient ischemic attack (TIA)				
- Other				
Favorable outcome (mRS 0 to 2) - % n/N				
- NIHSS** 1 to 9				
- NIHSS 10 to 30				
Favorable outcome (mRS 0 to 2) - % n/N				
- time to treatment 0 to 6 h				
- time to treatment 6 to 12 h				
- time to treatment 12 to 24 h				

*mRS, denotes modified Rankin Scale.

**NIHSS denotes National Institutes of Health Stroke Scale.

### Discussion

The aim of our study is to investigate whether preventive antibiotic therapy improves functional outcome by reducing the number of infections in acute stroke patients. With this SAP, we present the analyses that will be published in the primary publication. By publishing the statistical analysis plan before knowledge of any outcome, we stimulate transparency of scientific conduct and allow others to add timely suggestions for additional analyses.

Patients in the acute phase of stroke are at risk for infections. A systematic review and meta-analysis of 87 studies showed that infections complicate stroke in 30% of all stroke patients. Pneumonia was associated with mortality with an OR of 3.62 (95% CI 2.80 to 4.68)
[3]. The effect of preventive antibiotic therapy on outcome in stroke patients has been investigated in few studies. Two meta-analyses of these studies showed that preventive antibiotic therapy reduced the number of infections
[4, 5]. The proportion of patients who died and the number of disabled patients were not significantly reduced, but numbers of included patients were small.

The PROBE design with open-label preventive antibiotics might introduce detection bias for infection. Physicians are aware of the treatment allocation, which potentially influences decisions on nonscheduled treatment (that is, the detection and treatment of patients with infection). This might influence the outcome measure of infection rate. To control for this bias, we will provide a secondary judgement of infection diagnosis by a blinded expert panel, according to CDC criteria. The CDC criteria are restrictive and use ancillary investigations such as blood tests, chest X-rays and culture results to confirm the diagnosis of infection. In clinical practice, for a stroke patient with fever, a cough and abnormalities on auscultation, a physician will often not wait for culture results or refrain from treating pneumonia when a chest X-ray does not (yet) show a consolidation.

Preventive treatment with ceftriaxone after stroke might improve outcome by preventing infections. A potential beneficial effect on functional outcome might be caused by a direct effect of prevention of infections in patients after stroke, most commonly pneumonia, but also by the result of decreased length of stay on the stroke unit of even in the hospital. A recent study of individual patient data in a meta-analysis of randomized trials of ventilator-associated pneumonia prevention showed that an overall attributable mortality of ventilator-associated pneumonia is 13%, which was mainly caused by prolonged exposure to the risk of dying due to increased length of ICU stay
[20]. Ceftriaxone also has neuroprotective properties, at least in animal studies of stroke, which may be mediated by increased expression and activity of the glutamate transporter
[21].

Antibiotics may induce overgrowth of antibiotic resistant pathogens in individual patients
[22]. In the general population, selective antibiotic pressure is an important determinant of emergence and dissemination of antibiotic resistance
[23, 24]. Previous clinical trials on preventive antibiotic therapy in stroke, antibiotic resistance patterns of bacteria cultured from patients with or without preventive antibiotics were similar, but numbers of patients were low
[25]. Previous work has showed that implementation of preventive antibiotics in the ICU did not increase resistance rates in an environment with low levels of antibiotic resistance
[26]. We will compare total antibiotic use in both treatment groups during hospital stay and collect stool specimens in a nested case control study that includes 300 patients.

During the course of the study we changed the analysis of primary outcome on the mRS from a dichotomized analysis toward an ordinal regression analysis. The ordinal regression analysis is increasingly used in stroke trials because of its higher efficiency
[27]. Importantly, our primary outcome (for example, functional outcome on the mRS) was not changed, and the assumptions used in the initial sample size calculation were maintained. By using ordinal regression analysis, the total sample size was lowered from 3,200 patients to 2,550 patients. Using this method enables us to reduce the number of patients without changing the assumptions on the magnitude of the effect on the primary outcome scale from the original sample size calculation.

## Abbreviations

CRF: Case Record Form
CONSORT: Consolidated Standards of Reporting Trials
DDD: defined daily dose’
ITT: intention to treat
LOCF: last observation carried forward
mRS: modified Rankin Scale
NIHSS: National Institutes of Health Stroke Scale
OR: odds ratio
PASS: Preventive Antibiotics in Stroke Study
PP: per protocol
QALYS: quality adjusted life years
SAE: serious adverse event
SAP: statistical analysis plan
SUSAR: suspected unexpected serious adverse reaction
TIA: transient ischemic attack
VAP: ventilator-associated pneumonia.
